### Sample size

According to the data of a randomised pilot study which involved 10 patients, the effect size based on the Functional Rating Scale (FRI) was calculated to be 1.83. Since the number of patients in the pilot study was few, we calculated the sample size for the current study using an effect size of 0.8. Considering the results of our previous article [18] and the results obtained from the pilot study we expect ultrasound to be more effective and have chosen a one-sided test to calculate the sample size. Assuming alpha and power to be 0.05 and 0.8, in a one-tailed test the total sample size needed is 42 (21 patients in each group). Accounting for 10% drop-out, the total number of patients required is 46 (23 patients in each group).

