### Outcome measures

Patient's specifications such as age, sex, body mass index, and pain history will be recorded in a demographic questionnaire at the baseline assessment. All primary and secondary outcome measures will be measured by the researcher at baseline, the final treatment session (after 4 weeks), and at a follow-up measurement after 3 months.

Primary outcome measures will be

• Functional disability due to LBP measured by the Functional Rating Index.

• Pain measured on a visual analogue scale (VAS)

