### Data collection and analysis

An intention-to-treat analysis will be performed. In the case of dropouts and withdrawals, the last recorded values for the main outcome measures will be used in the analysis. We will check if the two groups are similar for the most important demographic characteristics and all outcome measures at baseline. In case of finding any differences we will adjust for them in a regression analysis. Between-group differences in the change of scores of all outcome measures will be analysed using the Statistical Package for the Social Sciences (SPSS) version 17. We will consider whether the data meet parametric or non-parametric conditions. If parametric, ANOVA, independent and paired t-tests will be used and in case of non-parametric conditions we will use Kruskal-Wallis, Mann-Whitney and Wilcoxon signed-rank tests. All analyses will be performed blinded for treatment allocation.

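### Baseline is adjusted for only when an undefined difference is found; adjusting each outcome for its own baseline value as a fixed rule is more precise and needs no new data

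*Protocol article*

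**What the plan says.** The rule is in the protocol article, Data collection and analysis. It has three parts.

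- A check: "We will check if the two groups are similar for the most important demographic characteristics and all outcome measures at baseline".
- A trigger: "In case of finding any differences we will adjust for them in a regression analysis". No test, threshold or size defines a difference, and no covariate is named in advance.
- A default: "Between-group differences in the change of scores of all outcome measures will be analysed", with the tests given as "If parametric, ANOVA, independent and paired t-tests will be used" and rank tests otherwise. None of these tests carries a baseline covariate.

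No other section commits to adjusting for the baseline score. The Outcome measures section confirms that every primary and secondary outcome has a baseline measurement. The Sample size section fixes the planning values: "we calculated the sample size for the current study using an effect size of 0.8", and "Assuming alpha and power to be 0.05 and 0.8, in a one-tailed test the total sample size needed is 42 (21 patients in each group".

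**The concern.** Allocation follows a computer-generated schedule in sealed envelopes, so baseline differences between the arms arise by chance. Whether a variable happens to be imbalanced is a poor guide to whether it should be a covariate. What matters is how strongly it predicts the outcome, and for a pain or disability score its own baseline value is the obvious candidate. The stated rule uses that value only when it happens to be imbalanced.

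Two things are at stake. The first is precision: in most realisations the comparison falls back to the raw change score, which is noisier than a baseline-adjusted comparison. The second is prespecification: the covariate set for the primary outcomes is settled only after the baseline data have been inspected, against a criterion the protocol does not state. With about 21 evaluable patients per arm, and with recruitment described in the Discussion as one of the most challenging elements, precision that costs nothing is worth taking.

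**Working it through.** **Inputs from the protocol.** Effect size 0.8, one-sided alpha 0.05, power 0.80, 21 per arm (Sample size section); change scores as the default analysis (Data collection and analysis).

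**Assumptions.** The correlation r is not in the documents, so 0.3, 0.5 and 0.7 are used. Baseline and follow-up SDs are taken as equal and the data as normal. A difference is read as p < 0.05 on a two-sided t-test of that outcome's own baseline score. The protocol does not say whether 0.8 is in SDs of the follow-up score or of the change score, so both are shown.

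**Step 1: reproduce the plan's figure.** For a one-sided two-sample t-test with d = 0.8, the noncentral t distribution gives 21 per arm, 42 in total, with power 0.817. The stated 42 is reproduced.

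**Step 2: precision of the two analyses.** In units of the follow-up variance, the residual variance is

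- change score: 2(1 − r)
- ANCOVA: 1 − r²
- ratio, ANCOVA to change: (1 − r²) / [2(1 − r)] = (1 + r)/2

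This gives 0.65, 0.75 and 0.85 for r = 0.3, 0.5 and 0.7, so ANCOVA cuts the variance by 35%, 25% and 15%. Put as sample size, 42 × 0.65 = 27.3, 42 × 0.75 = 31.5 and 42 × 0.85 = 35.7 patients under ANCOVA carry about the information of 42 under the change score. The ratio is below 1 for every r < 1, and the gain shrinks as r approaches 1.

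**Step 3: power of the stated rule.** Simulation with 21 per arm and a one-sided 5% test. The rule is ANCOVA if the baseline p < 0.05, otherwise a t-test on change.

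| r | 0.8 in follow-up SDs: rule v always-ANCOVA | 0.8 in change-score SDs: rule v always-ANCOVA |
|---|---|---|
| 0.3 | 70% v 84% | 83% v 93% |
| 0.5 | 82% v 90% | 82% v 89% |
| 0.7 | 95% v 97% | 82% v 86% |

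At r = 0.5 the two readings are the same case, because 2(1 − 0.5) = 1; the one-point difference in that row is simulation error and rounding. The unadjusted change score alone has power of about 69%, 82% and 95% on the first reading and 82% throughout on the second. The conditional rule therefore recovers only about one point or less of what ANCOVA offers, because the trigger fires in only about 5% of trials.

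**Step 4: type I error.** With no treatment effect, the conditional rule rejects in about 4.4% to 4.8% of trials at a nominal 5% (simulation error of a few tenths of a point). It is slightly conservative.

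**Step 5: how many chance flags to expect.** A count from the protocol:

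- age, sex, body mass index and pain history: 4
- FRI and VAS: 2
- flexion and extension: 2
- EMG test: three muscles on both sides plus one biceps femoris make 7 channels; each has slope and intercept for median and mean frequency, so 7 × 4 = 28; holding time and the lumbar-angle slope bring this to 30

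The total is 38. If each were tested at 5%, 38 × 0.05 = 1.9 chance flags would be expected, whatever the correlation between variables. If all were independent, the chance of at least one flag would be 1 − 0.95^38 = 0.858, or 86%. Indices taken from the same EMG signals are unlikely to be independent, so 86% is close to an upper limit.

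**The case against.** The strongest reply is that the rule does little measurable harm. On the protocol's own one-sided test it already reaches 80% power in five of the six cells above; the exception is r = 0.3 with the effect in follow-up SDs. The trigger looks at baseline data and not at outcomes, the analysis is to be done blind to allocation, and type I error is not inflated. All of this stands, and it limits the point to precision and prespecification.

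It also rules out three stronger readings that a reader might infer.

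- *The choice decides whether the trial reaches 80% power.* It does so in only one of the six cells. A two-sided calculation makes the shortfall look larger, but it charges this rule with the separate question of sidedness.
- *An irrelevant covariate is almost certain to enter the primary model.* This needs 38 independent tests at a 5% threshold that the protocol does not name; the check may be a descriptive judgement. Nor does the protocol say that an imbalanced EMG index would enter the FRI or VAS model.
- *The data-driven choice produces false positives.* The simulated rule shows the opposite tendency.

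What the reply does not meet is that always-ANCOVA has higher power in every cell, and that the protocol leaves both the criterion and the covariates open.

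**Conclusion.** The point holds as an improvement to a stated rule that costs almost nothing. Adjustment triggered by an undefined baseline difference selects covariates by chance and forgoes precision available from data already collected. On the planned one-sided test with 21 per arm, the power given up is about 2 to 14 percentage points over r = 0.3 to 0.7 if the effect size is in follow-up SDs, and about 4 to 10 points if it is in change-score SDs. The size rests on the assumed r, on equal SDs and on reading a difference as p < 0.05. The direction holds in large samples for any r below 1. The harm is lost precision and a covariate set that is settled only after the baseline data are seen. It is neither an inflated false-positive rate nor a demonstrated failure to reach the planned power.

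**What to change.** In Data collection and analysis:

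1. Make ANCOVA the between-group analysis for FRI, VAS and each secondary outcome, with treatment as factor and that outcome's own baseline value as covariate, whatever balance is observed.
2. Tabulate baseline characteristics by arm, but do not use the table to trigger adjustment.
3. Name any further covariates before the data are seen, chosen for prognostic value.
4. Revise the sentences on change scores, t-tests/ANOVA and non-parametric tests so that they do not contradict item 1. One option is to keep the rank-based tests as a sensitivity analysis.

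The cost is a short rewrite of that section. No new data, patients or measurements are needed.

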## Methods

### Study design

A single blind randomized controlled trial in which participants with chronic LBP will be randomized to one of two treatment groups:

• Continuous ultrasound + semi-supervised exercise therapy

• Sham ultrasound + semi-supervised exercise therapy

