### Randomization

Opaque, sealed envelopes will be prepared to the total number of patients using a computer generated randomization schedule, with half of the envelopes being allocated to each group ensuring equal number of subjects in each group.

The list and the envelopes will be prepared by a statistician who is not involved with the study prior to commencement of the trial to ensure concealment of patient allocation.

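### The tests are chosen from a data-dependent menu with baseline adjustment only on observed imbalance; one baseline-adjusted between-group analysis per outcome should be fixed in advance, and within-arm tests made descriptive

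*Protocol article*

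**What the plan says.** All references are to the protocol article.

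- **Design (Study design; Randomization).** There are two arms: "participants with chronic LBP will be randomized to one of two treatment groups". Allocation is equal. Both arms receive the same semi-supervised exercise programme.
- **Visits (Outcome measures).** Every outcome is measured at baseline, at the last treatment session and at one follow-up.
- **Comparison (Data collection and analysis).** The stated comparison is the difference between arms in change from baseline, for all outcomes.
- **Choice of test (same section).** "We will consider whether the data meet parametric or non-parametric conditions". No criterion is given. The menu follows: "If parametric, ANOVA, independent and paired t-tests will be used and in case of non-parametric conditions we will use Kruskal-Wallis", together with Mann-Whitney and Wilcoxon signed-rank. No test is tied to a question or a visit, and the within-arm tests are not marked as descriptive.
- **Adjustment (same section).** Regression adjustment is used only for characteristics or outcomes on which the arms are found to differ at baseline.
- **Safeguard (same section).** The analyses are to be done blind to allocation.
- **Sizing (Sample size).** "we calculated the sample size for the current study using an effect size of 0.8", and the authors "have chosen a one-sided test to calculate the sample size". This gives 21 per arm, or 23 with allowance for drop-out.

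**The concern.** Three features of the analysis paragraph work against the comparison it names.

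1. **Within-arm tests stand beside between-arm tests.** A paired t-test or signed-rank test asks whether an arm has changed from its own earlier values. Both arms exercise, and the Exercise therapy section itself describes exercise as slightly effective for pain and function. Improvement in both arms is therefore expected even if ultrasound adds nothing. If one arm reaches significance and the other does not, that is easily reported as a treatment effect, although it is not a test of one.

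2. **The menu contains redundant tests and an open choice.** With two arms, Kruskal-Wallis duplicates Mann-Whitney and one-way ANOVA duplicates the two-sided t-test. One outcome can thus yield several p-values, and nothing says which counts.

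3. **Baseline adjustment is conditional.** Baseline values are collected for every patient but enter a regression only if an imbalance is seen. In a trial of 46 patients this gives up precision that costs nothing.

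**Working it through.** **Inputs from the document:** two arms; d = 0.8; alpha 0.05, one-sided; power 0.80; 21 per arm before drop-out.

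**Assumptions, because the document gives no figures:** baseline-outcome correlation r of 0.3, 0.5 and 0.7; the planning effect of 0.8 expressed on the change-score SD; equal variances at baseline and follow-up; within-arm improvement of 0.3 to 0.6 SD of change.

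**Step 1. The plan's own figure.** A two-sample t-test with d = 0.8, one-sided 0.05 and 80% power needs 20.03 per arm, rounded up to 21, so 42 in total. This reproduces the plan. Power at 21 per arm is 81.7% one-sided and 71.6% two-sided.

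**Step 2. Redundancy.** In one simulated data set with 21 per arm, Kruskal-Wallis and the two-sided Mann-Whitney test (large-sample form, no continuity correction) both gave p = 0.2224. One-way ANOVA and the two-sided t-test both gave p = 0.2509. With two groups these pairs are the same tests.

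**Step 3. Within-arm tests when ultrasound has no effect.** Let both arms truly improve by e SDs of change. The power w of a two-sided paired t-test in one arm comes from the noncentral t distribution with 20 degrees of freedom and noncentrality e × √21. The arms are independent, so

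P(exactly one arm significant) = 2w(1 − w), and P(ultrasound arm only) = w(1 − w).

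| e | w | Exactly one arm | Ultrasound arm only |
|---|---|---|---|
| 0.30 | 0.258 | 38% | 19% |
| 0.45 | 0.501 | 50% | 25% |
| 0.60 | 0.744 | 38% | 19% |

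Outside this range the risk is smaller. At e = 0.2 exactly one arm is significant in 24% of trials, and at e = 0.8 in 12%.

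**Step 4. Gain from always adjusting for baseline.** With unit variance at each visit, a change score has variance 2(1 − r) and a baseline-adjusted outcome has variance 1 − r². The ratio is

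(1 − r²) / [2(1 − r)] = (1 + r)/2.

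An effect of 0.8 on the change-score SD becomes 0.8 / √((1 + r)/2) on the adjusted scale. Two-sided noncentral t power at 21 per arm is then:

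| r | (1 + r)/2 | Adjusted d | Power, change score | Power, adjusted |
|---|---|---|---|---|
| 0.3 | 0.65 | 0.992 | 72% | 88% |
| 0.5 | 0.75 | 0.924 | 72% | 83% |
| 0.7 | 0.85 | 0.868 | 72% | 78% |

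The degree of freedom spent on the covariate (39 instead of 40) does not alter these rounded figures.

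**Step 5. Cost of the data-dependent choice itself.** In simulation with 21 per arm and 10,000 runs, a mechanical rule (Shapiro-Wilk test, then t or Mann-Whitney) had one-sided type I error of 5.0% with normal data and 5.1% with skewed data. Taking the smaller of the two p-values freely gave 5.7% and 7.0%.

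**The case against.** The best defence is that the paragraph does name a between-group comparison of change scores, and that two tests on its list, the independent t-test and Mann-Whitney, suit two arms at a single visit. Kruskal-Wallis on two arms is valid, only superfluous. This stands: the menu contains usable tests, and the point is not that the planned comparison is invalid.

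A reader might go further and infer that the planned ANOVA dilutes the effect, because a group main effect over three visits averages in a baseline at which no effect can exist. That calculation gives two-sided power of 54% (r = 0.5) or 47% (r = 0.7) when d = 0.8 is on the raw-score SD. The document does not support this reading. It specifies change scores, which have already subtracted baseline, and nowhere describes a raw-score main effect over three visits. The figure also depends heavily on scale: with d on the change-score SD it is 78%, 54% and 31% at r = 0.3, 0.5 and 0.7.

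Nor should the normality check be presented as a serious type I error problem. Applied mechanically it does almost no harm (Step 5), and blinding to allocation limits selection by favoured direction. It does not prevent selection by p-value, since coded arms still show which test is significant, but the inflation there is modest.

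It can also be said that the paragraph never makes within-arm tests the basis for a claim of efficacy. That is true, so Step 3 measures a hazard of misreading and not a stated error of inference. But the tests are listed with the between-arm tests and nothing sets them apart.

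Finally, an article may leave model detail to a fuller plan. The objection here is to what the article does commit to: a choice of test without a criterion, and adjustment triggered by observed imbalance. A fuller plan would have to replace those commitments, not just add to them.

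**Conclusion.** The point holds as a worthwhile improvement to the analysis, not as a fatal flaw. The test family depends on the data without a criterion, Kruskal-Wallis adds nothing, and the within-arm tests do not estimate the effect the trial is meant to measure. Read side by side when ultrasound has no effect, they would show exactly one significant arm in about 38% to 50% of trials, given an assumed improvement of 0.3 to 0.6 SD of change in both arms.

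Always adjusting for baseline raises two-sided power at 21 per arm from 72% to between 78% and 88%, for assumed correlations from 0.7 down to 0.3. The 72% is two-sided, whereas the plan sized a one-sided test with 81.7% power. That gap comes from sidedness and is not charged to the test menu. If last values are carried forward for all 23 per arm, as the analysis section provides, the two-sided starting point is 76% instead of 72%.

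**What to change.** Replace the test-menu sentences and the conditional-adjustment sentence in Data collection and analysis with the following commitments:

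- For each outcome, one between-group analysis at each post-baseline visit: a linear model (ANCOVA, or a mixed model covering both visits) always adjusted for the baseline value of that outcome, reporting the difference between arms with a 95% confidence interval.
- The model applies whatever a normality check or a baseline comparison shows.
- A rank-based or bootstrap analysis is kept as a sensitivity analysis.
- Kruskal-Wallis is deleted.
- Within-arm changes are reported descriptively, without p-values.

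The cost is a change of wording made before the data are analysed. Baseline values are already collected for every outcome, the sample size need not rise, and fewer tests are run than now.

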## Discussion

The fact that there are more than 20 types of treatment for chronic LBP, each of which has multiple subcategories, is a testament that no single approach has yet been able to demonstrate its definitive superiority [34]. For example, exercise therapy is one promising treatment option, but there is still no consensus upon which kind is the most effective [9]. This situation makes it very challenging for clinicians, policy makers, insurers, and patients to make decisions regarding which treatment is the most appropriate for chronic LBP.

Despite the widespread use of therapeutic ultrasound as one of the most popular and commonly used modalities in the field of physiotherapy for LBP patients, there is still limited evidence of its effectiveness. Only a few RCTs have investigated the effect of ultrasound in treating patients with chronic LBP; often with varying methodology qualities and very small sample sizes, and have not been able to provide evidence regarding its usefulness.

The RCT we have described will evaluate the effectiveness of therapeutic ultrasound in addition to exercise therapy in patients with chronic LBP. The advantages of this study would be comparing the ultrasound with placebo ultrasound, which would clarify the value of adding ultrasound to a semi-supervised exercise program. Limited possibilities for double blinding can be a potential limitation to this study. Meanwhile we will evaluate potential bias by asking the patients whether they think they received real or sham ultrasound on the last treatment session. Recruiting a sufficient number of patients will be one of the most challenging elements of this study since it will be conducted without substantial funding.
